## Abstract

Patellofemoral pain (PFP) is a chronic condition that presents with patellar pain during various daily and recreational activities. Individuals with PFP have a wide range of impairments that result in long-term disability and reduced quality of life. Current interventions target hip muscle weakness with strength-based exercises, but recurrence rates are as high as 90%. A single feasibility study demonstrated success with power-based exercises; however, there is limited evidence evaluating pain or self-reported function in larger cohorts, and no study has assessed recurrence rates. This protocol details a study evaluating a strength-based rehabilitation programme compared with a strength-based programme incorporating power-based exercises in individuals with PFP. This single-blinded randomised controlled trial will evaluate 88 participants with PFP, aged 18–40 years old. Participants will be recruited from three universities, the surrounding community and sports medicine clinics. Participants will receive three telemedicine rehabilitation sessions a week for 6 weeks. The rehabilitation programme will consist of either strength-based exercises or a combination of power and strength-based exercises. Pain, subjective function and recurrence rates will be assessed at baseline, immediately after the intervention and at four follow-up time points: 6-month, 12-month, 18-month and 24-month postintervention. We will also assess neuromuscular function of the hips and global rating of change at each postintervention time point. Trial registration number NCT05403944.

WHAT IS ALREADY KNOWN ON THIS TOPICClinicians commonly prescribe strength-based rehabilitation programmes to treat patellofemoral pain; however, many patients do not demonstrate improvements in strength.Individuals with patellofemoral pain are not satisfied with their knee function within months after completing rehabilitation and report disability for years after treatment.WHAT THIS STUDY ADDSProvides information if incorporating power-based exercises compared with strength-based exercises are more effective at improving pain, self-reported function and neuromuscular function of the hip muscles in individuals with patellofemoral pain.Provides evidence if a rehabilitation programme with power-based exercises reduces the recurrence rates of patellofemoral pain for 2 years after treatment.HOW THIS STUDY MIGHT AFFECT RESEARCH, PRACTICE OR POLICYThis study would be a paradigm shift in the type of exercises prescribed to individuals with patellofemoral pain, as power-based exercises are limited in the literature and clinical practice.

## Introduction

Patellofemoral pain (PFP) is one of the most common knee pathologies in the general population and military personnel.^1^ The incidence of PFP in the military ranges from 9.7 to 571.4 per 1000 person-years, with females at 2.2 times greater risk than males.^1 2^ The annual prevalence rate in the general adult population is 22.7%.^1^ PFP accounts for 7% of all diagnoses in patients who seek medical care^3^ and up to 25% of all treatment for knee-related injuries within sports medicine clinics.^4^ Persistent knee pain, disability and impaired joint-related and health-related quality of life are common in individuals with PFP.^5 6^

The aetiology of PFP is unknown. Increased stress on the patellofemoral joint due to altered lower extremity mechanics is proposed to be the primary mechanism of PFP.^7^ Altered movement patterns are common in individuals with PFP during tasks, such as single-leg squat, stair ambulation and running,^8 9^ and are associated with greater knee pain and worse subjective function.^10^ Hip musculature is a major influence on the control of these lower extremity mechanics, and adults with PFP are 20%–28% weaker in hip strength when compared with asymptomatic adults.^11 12^

Clinicians prescribe strengthening exercises focused on weak gluteal muscles,^13 14^ which produces positive short-term outcomes but suboptimal long-term outcomes. Over 90% of patients with PFP report knee pain and symptoms greater than 15 years following initial diagnosis.^6^ While most patients with PFP seek medical care,^8^ over 60% are not satisfied with their knee function within 3 months of concluding treatment.^15^ Numerous studies targeting hip abductor strength produce minimal improvements,^16^ and hip strength gains are lost within months of concluding treatment.^16 17^

The lack of strength changes after hip-focused strengthening interventions suggests that there may be additional meaningful factors of neuromuscular function in adults with PFP. Rate of torque development (RTD) quantifies one’s ability to develop force rapidly and is sensitive at detecting chronic neuromuscular dysfunction.^18^ Adults with PFP have significant gluteal RTD deficits (55%) compared with asymptomatic adults, which represents almost twice the muscle function deficit when compared with strength measures (20%–28%).^19 20^ Not only does RTD better identify deficits in hip muscle function, RTD also more closely resembles demands of various functional tasks compared with isolated hip strength.^21^ RTD is an important measure of neuromuscular function in individuals with PFP that clinicians need to target during treatment.

Since gluteal RTD deficits are greater than strength deficits, interventions need to be developed specific to those deficits. Power-based exercises, which require a heavy resistance being conducted at a high peak force, are one intervention that has supportive evidence to improve RTD.^18^ Power-based exercises are more effective at enhancing RTD than strength-based exercises in adolescents, elderly and various pathological populations.^22 23^ To date, only a single feasibility study has evaluated the effect of power-based exercises on individuals with PFP.^24^ Power-based exercises targeting hip muscles successfully improved self-reported function, reduced pain and improved hip abduction and extension strength and power.^24^ Yet, this study only included 10 participants, did not include a strength-training comparison group and reported low adherence (33%) during weeks 7–12 of the intervention.^24^ Low adherence in late stages reduces the clinical applicability of the findings and negatively impacts the understanding of adequate dosage of power-based exercises for the treatment of PFP.^24^ Therefore, it is essential to conduct a randomised controlled trial (RCT) with a larger sample to overcome the limitations that reduce the clinical applicability.

### Aims and objectives

The proposed study will compare a strength-based rehabilitation programme, the standard of care (SOC), to strength training rehabilitation incorporating power exercises (STRIPE). The exercises in both groups will target the hip abductors, hip extensors, core and quadriceps muscles. Our primary outcomes are self-reported knee pain measured by the Visual Analogue Scale (VAS), self-reported function measured by the Anterior Knee Pain Scale (AKPS) and recurrence rates. Recent evidence suggests that two in every three individuals with PFP report symptoms up to 2 years after seeking care^25^; therefore, we will assess PFP recurrence rates for 2 years. The proposed interventions target gluteal muscle function, which will be collected as secondary outcome variables (hip RTD and frontal plane kinematics).

### Study hypothesis

The study hypothesis is that participants assigned to the STRIPE group will have a greater decrease in pain, greater improvements in self-reported function and lower PFP recurrence rates compared with those in the SOC group. Additionally, participants in the STRIPE group will have greater improvement in hip RTD and frontal plane kinematics compared with SOC.

## Methods

### Study design

This is a single-blinded RCT with two interventions, SOC and STRIPE. We adhered to the Standard Protocol Items: Recommendations for Intervention Trials checklist for this report (online supplemental file 1).^26^

10.1136/bmjsem-2022-001482.supp1Supplementary data

### Patient and public involvement

There was no formal involvement for patients or public individuals in the development of this study design.

### Setting

We will conduct this trial in three laboratories, the Sports Optimisation and Rehabilitation Laboratory at the University of Connecticut, Storrs, Connecticut, USA; the Rehabilitation, Athletic assessment & Dynamic Imaging Laboratory at the University of Central Florida, Orlando, Florida, USA; and the Motion Analysis & Integrative Neurophysiology Laboratory at the University of Toledo, Toledo, Ohio, USA.

### Eligibility and screening

Participants will be sought through flyers, social media posts, sports medicine physician referrals, and participation in previous PFP studies. Participants will be 18–40 years old and screened for eligibility with the inclusion/exclusion criteria defined by the Patellofemoral Pain Consensus statement^27^ (box 1). The intervention will be delivered through telemedicine, requiring participants to have a computer with internet access and camera/audio capabilities. Each site’s principal investigator (site-PI) will screen participants to ensure eligibility and consent participants. The three investigators at each site will complete an eligibility training and screening procedures session before participant enrolment.

Box 1Inclusion and exclusion criteriaInclusion criteriaInsidious onset of peripatellar or retropatellar pain greater than 3 months.Worst pain in the previous month of 3/10 with two of the following tasks:Prolonged sitting.Jumping.Squatting.Kneeling.Running.Stair ambulation.Exclusion criteriaOther forms of anterior knee painOsgood-Schlatter.Tendon pain.Bursitis.History of lower extremity surgery.History of patella subluxation.Meniscal injury, assessed by clustered special tests: history of ‘catching’ or ‘clocking’, pain with forced hyperextension, pain with maximal knee flexion, pain with McMurray test and joint line tenderness.Ligamentous instability, assessed by the anterior drawer, Lachman, posterior drawer, varus/valgus stress tests.Referred pain from the lumbar spine.Mental capacity for human subjects to consent to participating in the study.

### Randomisation, blinding and treatment allocation

Participants will be assigned to a treatment group by block randomisation, with a computer-generated online research randomiser (http://www.randomizer.org), completed by the statistician ([name]) prior to study enrolment. We will use a four-block randomisation approach for each clinical site, to ensure equal groups across sites. The University of Connecticut site will enroll 44 participants, resulting in 11 equal blocks of randomisation. The University of Central Florida and University of Toledo will each collect 22 participants, resulting in five 4 blocks of randomisation and a final block of 2 participants to allow for equal randomisation. An additional four-block randomisation was provided for each site in the instance a participant was assigned to a group but dropped out before any study data were collected. Group assignment will be maintained with a master list and allocation concealed from the site-PIs.

The proposed study will include blinding the research members conducting the baseline and postintervention assessments from group allocation, while separate team members will perform all treatments and will not conduct baseline or postintervention assessments. The participants will not be blinded, as reviewing the informed consent will outline group differences. To control for selection bias, the randomisation will be completed by the statistician who will not be directly associated with data collection or intervention. Additionally, the statistician will oversee randomisation with concealed allocation in opaque envelopes that will only be opened after baseline testing. Participants will be assigned a random participant number per site, maintained in an encrypted and secure document by site-PIs, ensuring confidentiality. We will also collect numerous secondary variables, such as psychological factors, coping strategies, physical activity and lifestyle factors, which we aim to reduce bias by using them as covariates if they influence the primary outcomes.

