Rest between sessions	Minimum of 48 hours	Minimum of 24 hours

The intervention sessions will be administered through supervised telemedicine to expand access for participants. The telemedicine sessions will allow the research team to facilitate supervision, progress exercises, individualise the exercise components and assess adherence of all sessions. The research team will provide individualised care from a private laboratory space and participants will complete sessions at their location of choice. All sessions will be delivered individually, and each session will be scheduled between the research team and participant. Telemedicine sessions will be conducted on their university sponsored platform (WebEx, Zoom, Teams) and will use password protection and waiting rooms to protect participant privacy. We will not record or store any electronic protected health information during the sessions to protect HIPAA. The research team administering the intervention are licensed athletic trainers or credentialed physical therapists with multiple years of clinical experience treating musculoskeletal conditions, including PFP. All research team members administering the intervention will complete training by the PI prior to enrolment. Training will include exercise descriptors, exercise feedback in a telemedicine format, progression/regression instructions, recording adherences and monitoring adverse events. The PI will complete fidelity assessments on the training topics every 3 months. Research team members will provide verbal encouragement to participants, monitor adherence and record session data (sets, repetitions, exercises, resistance, pain and exertion).

Exercise progression or regression will be individualised to the participant’s daily pain level and perceived effort with the modified rate of perceived exertion (RPE) scale (0—very light activity to 10—maximal effort). The target goal is pain less than 3/10 on the VAS and participants reporting between 7 and 9 on the RPE scale. Participants who report pain greater than 3/10 on a specific exercise will regress by reducing load or the exercise. Participants who report pain less than 3/10 and less than 7 on the RPE scale will progress the exercise by increasing resistance or advancing the task. No additional criteria for discontinuation or modifying the intervention will be administered; however, participants may elect to withdraw from the study at any time and the reason for withdrawal will be requested.

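### Fixed, published blocks of four within site would let anyone who learns a site's past allocations know about 34% of all allocations in advance; block sizes should vary and be withheld

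*Protocol article*

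**What the plan says.** The section on randomisation, blinding and treatment allocation in the protocol article sets the scheme: "We will use a four-block randomisation approach for each clinical site, to ensure equal groups across sites". It then gives the layout by site. For the largest site: "The University of Connecticut site will enroll 44 participants, resulting in 11 equal blocks of randomisation". For each of the other two, with 22 participants, it describes the scheme as "resulting in five 4 blocks of randomisation and a final block of 2 participants to allow for equal randomisation". Each site also has one reserve block of four.

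The same section lists safeguards. A statistician outside data collection and treatment prepares the list. Allocation is concealed from the site principal investigators. Envelopes are opaque and stay closed until baseline testing is done. Those who assess outcomes are blinded, and a separate team treats.

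On who knows what, the section says: "The participants will not be blinded, as reviewing the informed consent will outline group differences". Under Eligibility and screening, each site's principal investigator "will screen participants to ensure eligibility and consent participants". Under Intervention, one programme has three strength sessions a week and the other has two power sessions and one strength session. The same section adds: "The PI will complete fidelity assessments on the training topics every 3 months".

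Nothing says that block sizes vary or are kept from site staff, and the article itself makes the layout public.

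**The concern.** A block of constant, known size can be solved from its own history. Once one arm has used its places in a block, the rest of that block is fixed. An opaque envelope hides the next card but not this arithmetic, so concealment depends wholly on past allocations at a site never reaching anyone who affects entry.

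The treating staff are the weak link. They deliver visibly different programmes, so they must know each participant's arm. The article does not say this in words, but it follows from the two weekly schedules. With 22 or 44 participants per site, informal talk could carry that knowledge to someone involved in screening or scheduling.

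Selection bias is at stake. If the next arm can be foreseen, borderline candidates can be admitted, turned away or delayed, consciously or not, so that the arms differ in prognosis at entry. Adjusting for the baseline value of an outcome, as the planned MANCOVA does, would absorb part of such a difference but not the unmeasured part. For the recurrence analysis, the section on statistical analyses names only group and site terms.

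**Working it through.** **Inputs** (randomisation section unless noted)
- Block size 4 within each of three sites. Allocation is 1:1 within a block, read from the stated aim of equal groups.
- Site sizes 44, 22 and 22. Total 88 (Abstract).

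**The plan's own layout.** 11 × 4 = 44, and 5 × 4 + 2 = 22 at each of two sites. 44 + 22 + 22 = 88, so the stated total is reproduced. There are 11 + 5 + 5 = 21 blocks of four and 2 blocks of two. The article gives no predictability figure.

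**Allocations known with certainty, given all earlier ones in the block**
- Block of four: there are six balanced orders. The fourth place is always determined. The third is determined when the first two are alike, which is 2 of 6 orders. Expected number: 1 + 1/3 = 4/3.
- Block of two: the second place is always determined. Number: 1.

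| Site | Expected number known | Share |
|---|---|---|
| 44 participants | 11 × 4/3 = 14.67 | 33.3% |
| 22 participants (each of two) | 5 × 4/3 + 1 = 7.67 | 34.8% |
| All | 21 × 4/3 + 2 × 1 = 30 | 30/88 = 34.1% |

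The possible range over all lists is 21 + 2 = 23 (26.1%) to 42 + 2 = 44 (50%). The central 95% of random lists give 26 to 34 (29.5% to 38.6%). If all three reserve blocks were used, the expectation would be 30 + 3 × 4/3 = 34 of 100.

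**Best-guess hit rate** (always guess the arm with more places left)
- Block of four: 1/2 + 2/3 + 2/3 + 1 = 17/6.
- Block of two: 1/2 + 1 = 3/2.
- Total: 21 × 17/6 + 2 × 3/2 = 62.5, and 62.5/88 = 71.0%, against 50% by chance.

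**Effect of hidden, randomly varying sizes.** Simulation with 1000 lists per setting and all sizes in a set equally likely. The observer knows every past allocation and the set of sizes, but not where blocks begin and end. The two figures in each cell are for a site of 44 and a site of 22.

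| Sizes | Known with certainty | Best-guess hit rate |
|---|---|---|
| 2, 4 | 10.8%, 10.4% | 72.0%, 71.9% |
| 4, 6 | 5.7%, 5.4% | 68.9%, 68.6% |
| 2, 4, 6 | 3.8%, 4.0% | 70.0%, 69.6% |
| 4, 6, 8 | 2.5%, 2.3% | 67.7%, 67.4% |

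As a check on the simulation, fixed blocks of four at a site of 44 gave 33.4%, against 33.3% exactly.

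**The case against.** The strongest reply is that the protocol conceals allocation from the very people who decide on entry. Site principal investigators screen and consent, and the article says that they do not see allocations. Assessors are blinded, the statistician stands apart from data collection and treatment, and envelopes open only after baseline testing. If all of this is kept, nobody who enrols can use the pattern. That stands, and it is why the 34% must be stated with its condition.

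Several stronger readings are tempting, and the document does not support them:
- A reader might infer that a third of allocations are predictable as the design stands. They are predictable only to someone who knows the block size and every earlier allocation in the current block at that site.
- A reader might infer that unblinded participants know past allocations. Each knows only their own arm, sessions are delivered individually, and participants enrol nobody.
- A reader might infer that the quarterly fidelity assessments tell an enrolling investigator the arms. They concern training topics, and the article does not say that this principal investigator also enrols or receives a running list.
- A reader might infer that self-reported primary outcomes make the problem worse. Selection bias acts through prognosis at entry, whatever the type of outcome. Self-report by unblinded participants raises response bias, which varied block sizes would not touch.

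It is also fair to say that the remedy is partial, because the best-guess rate hardly moves. What remains is that none of the safeguards stops deduction once past arms leak. The section on eligibility also describes screening training for three investigators at each site. That wording is ambiguous, but screening may extend beyond those from whom allocation is expressly concealed.

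**Conclusion.** The point holds as a conditional risk. Fixed and published blocks of four within site leave 30 of 88 allocations (34.1%) expected to be known in advance to anyone at a site who has learnt the earlier allocations in the current block. Treating staff could meet that condition. The document does not show that anyone who influences entry does, and it shows no selection bias. The figure assumes 1:1 allocation within blocks and complete knowledge of the block's history.

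This is a low-cost improvement to the design. It is not a contradiction in the plan or a reason to doubt the trial as a whole.

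**What to change.** For participants not yet randomised, have the statistician reissue the site lists with randomly varying block sizes, for example 2, 4 and 6. Withhold the sizes from all site staff until enrolment closes. For the part of each list that is replaced, this cuts certain knowledge from about 34% to about 4%. It does not end informed guessing, so the present concealment from the site principal investigators and the blinding of assessors must stay.

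The cost is new lists and envelopes from the existing statistician, and some loss of exact balance within site. If enrolment stops three participants into a block of six, all three could be in one arm, a difference of three. At exactly 44 or 22 participants (even totals with even blocks) the difference would be at most two.

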### Demographics and outcome measures

Demographic variables (height, mass, age, sex, ethnicity, symptom duration, unilateral/bilateral symptoms) will be recorded at baseline. We will collect primary and secondary outcomes adhering to the study timeline (table 2). Participants will also complete a health history questionnaire, which includes questions related to previous treatment, pain location, aggravating factors, crepitus and pain quality. Baseline data, demographic variables and outcome measures will adhere to the REPORT-PFP checklist (Online supplemental file). We will instruct participants not to take pain medication for 48 hours prior to data collection of a primary outcome.^32^

**Table 2 T2:** Data collection timeline

		Baseline	Postintervention	6 months	12 months	18 months	24 months
Primary	Visual Analogue Scale	X	X	X	X	X	X
	Anterior Knee Pain Scale	X	X	X	X	X	X
	PFP recurrence			X	X	X	X
Secondary	Hip Rate of Torque Development	X	X				
	Fontal Plane Single Leg Squat Kinematics	X	X	X	X	X	X
Descriptive variables	PROMIS-10	X	X	X	X	X	X
	KOOS w/ PF-subscale	X	X	X	X	X	X
	Fear Avoidance Belief Questionnaire	X	X	X	X	X	X
	Pain Self-Efficacy Questionnaire	X	X	X	X	X	X
	International Physical Activity Questionnaire	X	X	X	X	X	X
	Global Rating of Change		X	X	X	X	X

KOOS, Knee injury and Osteoarthritis Outcome Score; PFP, patellofemoral pain; PROMIS-10, Patient-Reported Outcomes Measurement Information System-10.

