### Sample size

Power analysis for preintervention to postintervention differences was conducted with a Monte Carlo simulation involving 5000 replications of the data via the interval Monte Carlo simulation capabilities of Mplus V.8.6 for the multivariate analysis of covariance (MANCOVA) assuming: (1) standardisation of all analysis variables, (2) randomisation results in equivalent groups across the outcome variables at the baseline assessment, (3) homogeneity of covariate regression slopes (ie, 6-week postintervention outcome variables regressed onto their respective baseline assessment counterparts) will be ensured using parameter estimate equality constraints, (4) missing completely at random (MCAR) or missing at random (MAR) missing data were included in the simulation and ranged between 4.5% and 15.9% pairwise missing data (average=10%), (5) all six outcome variables were assumed to be intercorrelated at a medium effect size (ie, *r*_Pearson_=0.50), (6) baseline assessment scores for all six outcome variables, included as covariates, will explain (*R*^2^=0.20) 20% of 6-week postintervention variance, (7) maximum likelihood missing data handling will make N=88 available for analysis and (8) α=0.05 (two tailed). The power analysis question of interest was the smallest *d* incremental difference (*d*) at 6-week postintervention for STRIPE versus SOC participants detectable with power at 0.80. Power analysis results showed power would be >0.80 for any effect size difference between STRIPE and SOC participants of d>0.55.

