### Statistical analyses

We will use a MANCOVA to test for a significant treatment group (STRIPE vs SOC) main effect showing significantly greater improvement in each outcome variable at 6-week postintervention controlling for respective baseline values of each outcome variable. A multivariate intercept-only longitudinal SEM growth curve model will be used to determine if the difference in each outcome variable at 6-week postintervention is maintained at 6, 12, 18 and 24 months follow-up. The intercept-only SEM implies between-participant variability in the overall outcome variable, but the outcome does not change as a function of time. Finally, a binary logistic regression analysis will be used to determine if the intervention group (STRIPE vs SOC) significantly predicts PFP recurrence at the end of the 2-year follow-up. Dummy coded variables will be created and added to each analysis to account for cluster (site) differences and produce robust SEs. All missing data will be handled assuming MAR with maximum likelihood estimation consistent with currently accepted methodological research and practice.

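### The covariate rule lets the observed primary outcomes decide which variables enter the primary models, and it is not carried into the analysis or sample size sections

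*Protocol article*

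**What the plan says.** The rule stands at the end of Randomisation, blinding and treatment allocation: "which we aim to reduce bias by using them as covariates if they influence the primary outcomes". The stated purpose is to reduce bias. The candidates are an open-ended set of psychological, coping, activity and lifestyle measures, and no test, threshold, time point or model is given.

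Table 2 (Demographics and outcome measures) lists three instruments that clearly match the named constructs: the "Fear Avoidance Belief Questionnaire", the "Pain Self-Efficacy Questionnaire" and the "International Physical Activity Questionnaire". Each is scheduled at baseline and at all five later visits, and the table classes them as descriptive. No instrument is clearly matched to coping strategies or lifestyle factors.

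Statistical analyses describes the 6-week MANCOVA as "controlling for respective baseline values of each outcome variable", and adds for all models: "Dummy coded variables will be created and added to each analysis to account for cluster (site) differences". Sample size uses the same baseline adjustment: "baseline assessment scores for all six outcome variables, included as covariates", explaining 20% of postintervention variance. Neither section mentions further covariates or the selection rule.

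**The concern.** Whether a variable influences pain, function or recurrence in this trial can only be judged from the trial's outcome data. The rule therefore leaves the primary models open until those data are seen. With three primary outcomes it could also give three different covariate sets. For recurrence, analysed by logistic regression, adding prognostic covariates changes the odds ratio being estimated, so the target itself would depend on what was selected.

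The bias rationale is weak. Randomisation already removes systematic baseline confounding, and baseline covariates mainly add precision. Values measured after treatment are different: if the programme changes them, adjusting for them removes the part of the effect that runs through them. The rule does not say which kind of value is meant.

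**Working it through.** **Inputs from the article.** N=88, allocated equally (44 per arm); two-sided alpha 0.05; d=0.55; baseline R²=0.20.

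**Assumed, because the article gives no figure.** The number of candidates (3 or 5), their standardised slopes on the outcome (0 to 0.3 for baseline candidates), a p<0.05 screen, the shift a that treatment causes in a post-treatment candidate (0 to 0.5 SD), and that candidate's slope b on the outcome (0.3 or 0.5).

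**Step 1: reproduce the stated power.** The standard error is √(1−0.20) × √(2/44) = 0.894 × 0.213 = 0.191. Then 0.55/0.191 = 2.88, and power = Φ(2.88 − 1.96) = 0.82 (0.81 with the noncentral t). The stated power above 0.80 reproduces and serves as the base below.

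**Step 2: baseline candidates, no true effect.** ANCOVA simulations with 3,000 runs for three candidates and 1,500 for five. Type I error:

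| Candidates, slope | None added | p<0.05 screen | Most favourable subset |
|---|---|---|---|
| 3, 0.0 | 0.050 | 0.053 | 0.064 |
| 3, 0.2 | 0.049 | 0.056 | 0.089 |
| 3, 0.3 | 0.049 | 0.060 | 0.121 |
| 5, 0.2 | 0.043 | 0.059 | 0.125 |
| 5, 0.3 | 0.050 | 0.054 | 0.211 |

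The Monte Carlo standard error near 5% is √(0.05×0.95/3000) = 0.004 for three candidates and √(0.05×0.95/1500) = 0.006 for five. The mechanical screen lies 0.3 to 1.0 points above the nominal 5%. The largest gap from its own comparison column, 1.6 points, is in a row where that column happened to fall at 0.043. The last column is a different procedure: it fits every subset and keeps the smallest treatment p-value.

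**Step 3: one post-treatment candidate, true d=0.55.** 3,000 runs each, candidate kept if p<0.05. When it is always kept, the expected estimate is 0.55 − a×b.

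| a | b | Kept | Mean estimate | Power without it | Power under the rule |
|---|---|---|---|---|---|
| 0 | 0.3 | 89% | 0.55 | 0.81 | 0.85 |
| 0 | 0.5 | 100% | 0.55 | 0.80 | 0.93 |
| 0.2 | 0.3 | 89% | 0.50 | 0.82 | 0.76 |
| 0.2 | 0.5 | 100% | 0.45 | 0.82 | 0.80 |
| 0.3 | 0.3 | 89% | 0.47 | 0.81 | 0.70 |
| 0.3 | 0.5 | 100% | 0.40 | 0.81 | 0.68 |
| 0.5 | 0.3 | 89% | 0.41 | 0.79 | 0.56 |
| 0.5 | 0.5 | 100% | 0.30 | 0.81 | 0.44 |

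Check of the last row: 0.55 − 0.5×0.5 = 0.30. Check of the third row: 0.55 − 0.888×0.2×0.3 = 0.50. With a=0 nothing is removed and power rises.

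**The case against.** The strongest reply is that the article nowhere proposes post-treatment adjustment. Every covariate that it places in a model is a baseline value, and Table 2 shows when instruments are collected, not which values serve as covariates. A reader might infer from the repeated schedule that later scores will enter the primary models. The text does not support that; it only fails to rule it out. The larger losses in Step 3 also need a sizeable between-arm shift. Both arms receive the same number of supervised sessions, the same muscle groups and the same educational material, and nothing in the article indicates a difference as large as 0.5 SD in self-efficacy, fear-avoidance or activity.

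A reader might also see a flat contradiction between the rule and Statistical analyses. That goes too far. The latter section never says its list of terms is complete, so conditional additions are compatible with it. What stands is that a rule affecting the primary models is absent from the section that defines them and from the power calculation.

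Third, applied mechanically the rule does little harm to type I error. The 6% to 12% range needs a search for the best treatment p-value, which the article does not describe, so it is not the rule's expected effect.

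Finally, covariate detail is often left to a full protocol or analysis plan, which may settle the matter. That would excuse silence. Here the article states an outcome-dependent condition, which a later plan would have to overrule rather than complete.

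**Conclusion.** The point holds at moderate severity. What is established from the text is an outcome-dependent covariate rule with no defined test, closed candidate list or time point, which appears in neither the Statistical analyses nor the Sample size section.

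Its size depends on the reading:

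- **Fixed screen on baseline values:** about one point of type I error or less above 5%.
- **Free choice among three baseline candidates:** about 6% to 12%, a worst case. The list is open-ended, and five candidates would give about 12% to 21%.
- **Post-treatment values that treatment shifts:** at true d=0.55, an estimate of about 0.50 to 0.30 and power between 0.80 and 0.44 against about 0.80, depending wholly on the assumed mediation; no loss if there is no shift.

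The last two are conditional on uses that the article leaves open but does not announce.

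**What to change.** Delete the condition that covariates enter if they influence the primary outcomes. State in Statistical analyses that the primary models adjust for site and, where the outcome has one, its baseline value, plus any further baseline variables named before outcome data are seen. Limit covariates in the primary models to baseline values. Label any other adjustment as a sensitivity analysis, and any use of post-baseline fear-avoidance, self-efficacy or activity scores as exploratory mediation analysis.

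The cost is a few sentences, with no extra participants or data. A prognostic baseline covariate may even help: a covariate that treatment does not affect (the a=0 rows of Step 3) left the estimate at 0.55 and gave power of 0.85 to 0.93, against about 0.80 to 0.81 without it.
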